## Abstract

**Background:**

Many patients with Inflammatory Bowel Diseases (IBD) suffer from psychological distress, fatigue and sleep disturbances, which are associated with reduced quality of life (QoL) and increased societal costs. Only limited psychosocial treatment options are available. As Mindfulness-Based Cognitive Therapy (MBCT) has demonstrated to improve psychological distress, QoL and sleep in other populations, MBCT might also be effective in patients with IBD.

**Methods:**

The MindIBD study is a prospective, multicentre, randomised controlled trial comparing MBCT plus Treatment As Usual (TAU) versus TAU alone in a targeted number of 136 IBD patients in remission, aged 16 years and older with at least mild psychological distress (Hospital Anxiety and Depression Scale (HADS) total score ≥ 11). Primary outcome is reduction of psychological distress post-intervention, measured by the HADS. In addition, the effect of MBCT on sleep quality (including actigraphy and electroencephalography recordings), fatigue, disease activity, perceived disease control, QoL and positive mental health will be examined. Assessments will be conducted at baseline and at 3, 6, 9 and 12 months follow-up. Cost-effectiveness will be determined and a process evaluation will be conducted.

**Discussion:**

This study will provide valuable insight into the clinical effect of MBCT on psychological distress, sleep quality, fatigue and QoL in IBD patients and into the cost-effectiveness. If effective, MBCT can be a valuable addition to the available psychosocial interventions for patients with IBD. Moreover, findings from this study may also be applicable in patients with other chronic conditions.

**Trial registration:**

ClinicalTrials.gov: NCT04646785, registered on 30/11/2020.

**Supplementary Information:**

The online version contains supplementary material available at 10.1186/s40359-023-01127-0.

## Background

Inflammatory Bowel Disease (IBD), mainly consisting of Crohn’s disease and ulcerative colitis, is characterised by chronic relapsing inflammation of the intestinal tract. In the Netherlands, currently about 90,000 patients have been diagnosed with IBD and the prevalence seems to be rising worldwide [1]. The disease manifests mainly in young adults, aged between 15 and 30 years, who are in a turbulent part of their life, finding their way with housing, friends, education and perhaps starting a family and career. Physical symptoms include abdominal pain, diarrhoea, rectal bleeding and fatigue. Although the arsenal of drugs has increased in past decades, there is no cure for the disease and patients are usually treated with different (immunosuppressive) medications for a long time. Despite these treatment options, flares are common with cumulative rates of 69–93% after 5 years for patients with Crohn’s disease and 78–82% for patients with ulcerative colitis [2].

Besides physical symptoms, many IBD patients experience psychological distress, including symptoms of depression and anxiety. This could be due to its unpredictable course and prognosis, difficulties accepting their chronic disease and side effects of medication [3]. About a quarter of patients in remission experience depressive symptoms and about a third experience symptoms of anxiety, which is two to three times higher than healthy controls [4]. These numbers nearly double during flares [3, 4]. Psychological distress has been associated with a decrease in self-care and quality of life (QoL) and an increase in the experience of physical symptoms, including fatigue. Besides that, these patients are more likely to seek medical care, which leads to higher healthcare costs [3]. Moreover, the association between psychological distress and disease activity might be bidirectional, since it has been suggested that perceived psychological distress may affect the onset and course of IBD [5]. However evidence is scarce and inconsistent [5, 6].

In addition, many IBD patients suffer from fatigue, sleep disturbances and decreased QoL. In quiescent IBD, half of the patients experience fatigue, compared to 8% in a healthy population [7]. Across several countries, and in particular from the patient’s perspective, fatigue has been recognised as a key topic for research [8]. Moreover, patients with IBD report poorer sleep quality than healthy controls [9]. Sleep disturbances have been linked to disease activity and shown as a marker for subclinical inflammation and a risk factor for developing a flare [10]. It is therefore not surprising that IBD patients report lower QoL compared to the general population and this underscores the importance of finding appropriate treatment options that address these symptoms [11].

Mindfulness-based interventions (MBIs) have been shown to be effective in reducing psychological distress and fatigue, as well as improving sleep quality and QoL, both in patients with mental and somatic illnesses [12, 13]. MBIs are psychosocial group-based interventions that focus on the cultivation of mindfulness skills in order to better cope with negative, repetitive thoughts and feelings [14]. The effect of MBIs on psychological distress is potentially mediated by mechanisms such as mindfulness, self-compassion, rumination and worry [15]. Sleep quality might also play a role, given the association between poor sleep quality and psychological distress [16], and the positive effect mindfulness appears to have on sleep quality [13].

Although the available evidence on the effectiveness of MBIs for IBD is still relatively scarce, a meta-analysis, which included 477 patients in eight randomised controlled trials (RCTs), showed significant benefits in terms of psychological distress and QoL [17]. However, the variety in MBIs was rather high, none of the studies had psychological distress as primary outcome, and most studies suffered from methodological limitations such as small sample size, incomplete data reporting and a lack of fidelity measures. Looking specifically to the available RCTs using Mindfulness-Based Cognitive Therapy (MBCT) or Mindfulness-Based Stress Reduction (MBSR) in IBD patients, it was limited to two studies [18, 19]. Jedel et al. included patients with a recent flare of ulcerative colitis and found no difference in disease course between the MBSR and control groups, although patients in the intervention group experienced less stress during a flare in the follow-up period than those in the control group [18]. Schoultz et al. found a significant decrease in psychological distress and non-significant improvement of QoL and disease activity in patients with IBD allocated to MBCT compared to the waitlist control condition [19]. Two additional RCTs examining MBCT in IBD were conducted after the meta-analysis [20, 21]. Ewais et al. showed that depressed young adults with IBD were less depressed and stressed after MBCT, with an improvement in coping but not in QoL [20]. Finally, in a recent study of Bredero et al., fatigued IBD patients experienced significantly lower levels of fatigue after MBCT compared to the waitlist group [21]. In none of these studies sleep quality was an outcome of interest. Due to the limited evidence, it seems warranted to conduct further research to the effectiveness of mindfulness in patients with IBD, particularly focused on psychological distress and sleep quality.

The MindIBD study is a multi-centre RCT, using a variety of subjective and objective outcome measures. The trial primarily focuses on the effectiveness of MBCT in reducing psychological distress in patients with IBD. Besides that, we are also interested in the effects on sleep quality, fatigue, disease activity, perceived disease control, QoL and positive mental health. In addition, we will investigate the possibly mediating role of mindfulness, self-compassion and perseverative thinking. Eventually, cost-effectiveness will be examined and a process evaluation of implementing MBCT in IBD healthcare will be conducted.

## Methods

### Study design

The MindIBD trial is a prospective, multicentre, parallel-group RCT comparing MBCT plus treatment as usual (TAU) versus TAU alone. Assessments are conducted at baseline (T0) and at 3 (T1), 6 (T2), 9 (T3) and 12 (T4) months follow-up. To evaluate the feasibility for implementing MBCT in the care for patients with IBD, a process evaluation with qualitative interviews will be part of the project. The study protocol has been approved by the ethical review board CMO Arnhem-Nijmegen (#2021–7319; NL75762.091.20).

### Setting

Participants are recruited from the gastroenterology and paediatrics outpatient clinics of four Dutch hospitals, which consist of one university hospital (Radboud University Medical Centre, Nijmegen) and three general teaching hospitals (Jeroen Bosch Hospital (‘s-Hertogenbosch), Canisius Wilhelmina Hospital (Nijmegen) and Rijnstate Hospital (Arnhem)).

### Study population

The study population consists of patients of 16 years and older with a confirmed IBD diagnosis of Crohn’s disease, ulcerative colitis or indeterminate colitis. Additional inclusion criteria are: (1) IBD in remission (faecal calprotectin < 250 mg/kg [22]) for at least three months; (2) taking no IBD medication or being on a stable dose of aminosalicylates, immunosuppressants, biologics or small molecule therapy for at least three months prior to enrolment; (3) a Hospital Anxiety and Depression Scale (HADS) total score ≥ 11, which has been previously used to select somatically ill patients with elevated levels of anxiety or depression [23, 24]; and (4) a good understanding of the Dutch language. The following exclusion criteria are applied: (1) severe psychiatric disorders, e.g. acute suicidality, psychosis; (2) current alcohol or drug dependency; (3) anaemia (haemoglobin level range in men: 8.4–11.0 mmol/L and in women: 7.4–10.0 mmol/L); and (4) prior participation in an eight-week MBI.

### Procedure and assessments

Figure 1 provides a flowchart of the study procedure. In order to minimize the risk of selection bias by attending physicians, all IBD patients treated in these hospitals receive an invitation leaflet. Those interested in participation are referred to an online, anonymous pre-screening survey [25], which includes the HADS and questions about the main eligibility criteria. Probably eligible participants are guided to a registration form, after which they receive additional information about the trial and are invited for a research interview. During this research interview the study is explained in more detail, the inclusion and exclusion criteria are reviewed thoroughly and written informed consent is obtained (Appendix 1). Definite eligibility is determined after laboratory screening to rule out anaemia or elevated faecal calprotectin levels. After definite inclusion in the study, participants are invited for the baseline assessment, which consists of: (1) self-report questionnaires; (2) an interview in which demographic and disease characteristics are examined (age, sex, country of origin, level of education, marital status, employment status, body mass index, IBD type, medication use, age at onset of IBD, time since last flare, hospitalizations due to flare, comorbid psychiatric diagnoses); and (3) sleep analysis, using sleep electroencephalography (EEG) headband for three consecutive nights. From baseline until post-treatment, participants are asked to wear an actigraphy wristband for additional sleep data. At post-treatment, they are asked to sleep another three nights with the EEG headband. The post-treatment assessment (3 months after baseline) and the follow-up assessments (6, 9 and 12 months after baseline) consist of self-report questionnaires and an interview by clinician. The 6- and 12-month assessments include blood and stool samples for all participants. The 3- and 9-month assessment includes blood and stool samples only for patients with a suspected flare. Table 1 provides an overview of assessments and measures. The content of the outcome measures is explained below under the heading ‘outcome measures’.

**Fig. 1 Fig1:**
[figure not shown]
Flowchart of study procedure, based on CONSORT diagram

**Table 1 Tab1:** Overview of assessments and measures

	T0 (baseline)	MBCT	T1 (3 months)	T2 (6 months)	T3 (9 months)	T4 (12 months)
**Self-report questionnaires**						
*Psychological distress*						
HADS	✓		✓	✓	✓	✓
*Sleep quality and fatigue*						
PSQI	✓		✓	✓	✓	✓
ISI	✓		✓	✓	✓	✓
FACIT-F	✓		✓	✓	✓	✓
*IBD-related measures*						
SIBDQ	✓		✓	✓	✓	✓
IBD-control	✓		✓	✓	✓	✓
*Mental health-related measures*						
PTQ	✓		✓	✓	✓	✓
FFMQ-SF	✓		✓	✓	✓	✓
SCS-SF	✓		✓	✓	✓	✓
MHC-SF	✓		✓	✓	✓	✓
MAQ		✓	✓	✓	✓	✓
*Cost-effectiveness*						
TiC-P	✓		✓	✓	✓	✓
EQ-5D	✓		✓	✓	✓	✓
**Clinical interview**						
HBI/SCCAI	✓		✓	✓	✓	✓
Time to flare	✓		✓	✓	✓	✓
(S)AE	✓		✓	✓	✓	✓
**Clinical outcomes**						
Blood tests^*^	✓		(✓)	✓	(✓)	✓
Faecal calprotectin	✓		(✓)	✓	(✓)	✓
**Sleep analysis**						
Headband (*Zmax*)	✓		✓			
Wristband (*Fitbit*)	✓	✓	✓			

*Abbreviations*: EQ-5D, EuroQol-5D-5 L; FACIT-F, Functional Assessment of Chronic Illness Therapy-Fatigue; FFMQ-SF, Five Facet Mindfulness Questionnaire-Short Form; HADS, Hospital Anxiety and Depression Scale; HBI, Harvey Brashaw Index; IBD, Inflammatory Bowel Disease; ISI, Insomnia Severity Index; MAQ, Mindfulness Adherence Questionnaire; MBCT, Mindfulness-Based Cognitive Therapy; MHC-SF, Mental Health Continuum-Short Form; PSQI, Pittsburgh Sleep Quality Inventory; PTQ, Perseverative Thinking Questionnaire; (S)AE, (Serious) Adverse Events; SCCAI, Simple Clinical Colitis Activity Index; SCS-SF, Self-Compassion Scale-Short Form; SIBDQ, Short Inflammatory Bowel Disease Questionnaire; TiC-P, Trimbos iMTA Questionnaire for Costs associated with Psychiatric Illness

*Blood tests consists of haemoglobin, C-reactive protein and albumin. At baseline ferritin is added.

### Randomisation and blinding

Randomisation is computerised using CastorEDC [26], an Electronic Data Capture program complying with all regulatory guidance [27]. Participants are allocated using a 1:1 randomisation ratio scheme. Randomisation is stratified for hospital, sex and type of IBD. In order to ensure balanced groups, block randomisation with block sizes of either 2, 4 or 6 are used. Participants cannot be blinded to allocation. For reasons of coordination and logistics, randomisation is performed by a member of the research team, and the research team has therefore access to the information about the assigned group.

### Intervention: MBCT

The MBCT program is based on the protocol published by Segal, Williams and Teasdale [14]. The program consists of eight weekly 2.5 hour sessions, a six hour silent day between session 6 and 7, and daily home practice of 45 minutes guided by audio files. Groups consist of eight to ten participants. Materials are adjusted to include IBD-related examples. The course is offered in the cities where patients are treated (Nijmegen, Arnhem and ‘s-Hertogenbosch) and taught by qualified teachers according to the advanced criteria of the Association of Mindfulness-Based Teachers in the Netherlands and Flanders [28]. These criteria include a minimum of 150 hours of education in MBSR/MBCT (entailing theoretical background, skills practice, supervision and reflection), a minimum of three years of personal meditation practice and attending retreats, and providing a minimum of two courses per two years. All mindfulness teachers participated in a kick-off meeting before the start of the trial, in which the trial-specific MBCT protocol was discussed. Peer supervision meetings are organised twice per MBCT course during the intervention phase of the trial. Teaching sessions are recorded and a random sample of sessions will be rated by two independent raters using the Mindfulness-Based Interventions: Teaching Assessment Criteria (MBI:TAC) [29]. Participation of the training can be discontinued on participant’s request at any time. If so, the participant is encouraged to complete further assessments of the study.

### Comparator: treatment as usual

TAU consists of all healthcare that patients usually receive to treat IBD according to Dutch and European treatment guidelines [30–33]. These treatments mainly focus on pharmacological and surgical disease control and prevention of complications. TAU can also include non-mindfulness based psychosocial treatments. All healthcare use is registered (see outcome measures, cost-effectiveness). After the final assessment, participants of the TAU group will also be given the opportunity to participate in an MBCT course.

### Outcome measures

#### Primary outcome

#### HADS

The primary outcome is psychological distress at post-treatment, measured by a total score of the *HADS*, which was originally developed as a screening instrument for the possible anxiety and depressive states in medical out-patient clinics [34]. The questionnaire consists of 14 items of which 7 items are related to depression and 7 items are related to anxiety. Scores for each item ranges from 0 to 3, giving total scores between 0 and 42 (and maxima of 21 per subscale). Higher scores indicate higher levels of psychological distress. The internal consistency of the HADS-total in the Dutch version of the questionnaire has been shown to be good (Cronbach’s *α* = 0.82–0.90) [35].

#### Secondary outcomes

#### Sleep quality and fatigue

The *Pittsburgh Sleep Quality Inventory (PSQI)* is used to measure subjective sleep quality [36]. The PSQI consist of 19 items offering 7 component scores (subjective sleep quality, sleep latency, sleep duration, habitual sleep efficiency, sleep disturbances, use of sleeping medication and daytime dysfunction) and a composite score. Scores for each component range from 0 to 3 [36]. The overall PSQI score is then calculated by summing up the 7 component scores, providing an global score ranging from 0 to 21. Higher scores indicate worse sleep quality. Cronbach’s *α* has been shown to be acceptable (0.64–0.83) in different samples, including chronic diseases such as rheumatic arthritis (Cronbach’s *α =* 0.73) [37].

The 7-item *Insomnia Severity Index (ISI)* is used to measure insomnia, including questions about the nature, severity and impact [38]. A 5-point Likert scale is used to score each item, providing a total score ranging from 0 to 28. Higher scores reflect greater insomnia severity. The ISI has been shown to have a good reliability in quantifying perceived insomnia severity (Cronbach’s *α* = 0.70–0.92) [39].

Objective sleep quality is measured electrophysiologically using a 2-channel EEG headband (*Zmax, Hypnodyne*) and by indirect parameters using an actigraphy wristband (*Fitbit Activity Tracker, Google*). From the sleep EEG data, classical sleep scoring parameters [40] related to sleep quality can be derived: total sleep time (TST), time in bed (TIB: period from lights out/start recording to lights on/stop recording in minutes), sleep efficiency (SE: defined as the percentage of TST/TIB*100%), sleep onset latency (SOL: from lights out/start recording to first epoch of any sleep stage in minutes), wake after sleep onset (WASO: the number of minutes awake following the first three consecutive epochs of any sleep stage), absolute and relative duration of rapid eye movement sleep (REM sleep), and absolute and relative duration of deep sleep. Sleep stage analysis per 30 seconds epoch plus derived variables of the *Zmax* sleep EEG recordings will be performed semi-automatically using in-house software [41]. The following sleep scoring parameters can be derived from the *Fitbit *sleep data: TST, WASO, absolute and relative duration of REM sleep, and absolute and relative duration of deep sleep. Although polysomnography is the gold standard of measuring sleep, comparable two-channels sleep EEG headbands demonstrate good validity [42], and actigraphy via fitness trackers has been shown valid for screening purposes if applied repeatedly [43]. Currently, an in-house validation study of the *Zmax* is carried out.

The *Functional Assessment of Chronic Illness Therapy-Fatigue (FACIT-F)* is a measure to assess subjective fatigue and its impact on daily life [44]. The questionnaire consists of 40 items, divided into 13 items about fatigue and 27 items about four generic domains of health-related QoL (physical well-being, social/family well-being, emotional well-being and functional well-being) [45]. All items are scored on a 5-point Likert scale. Higher scores in the fatigue subscale (range: 0–52) indicate less fatigue. The four generic domains together reflect better quality of life, ranging from 0 to 108. The subscale fatigue can be used as a stand-alone questionnaire to assess subjective fatigue (Cronbach’s *α* = 0.93–0.95) [44], and has been shown excellent reliability in patients with IBD (Cronbach’s *α* = 0.94) [46]. The QoL-questions has been shown to be reliable in chronic diseases, such as multiple sclerosis (Cronbach’s *α* = 0.82–0.96) [47].

#### IBD-related measures

The *Short Inflammatory Bowel Disease Questionnaire (SIBDQ)* is used to measure IBD-related QoL [48]. The SIBDQ has 10 items scored on a 7-point Likert scale, grouped into bowel symptoms, systemic symptoms, emotional function and social function. Overall scores range from 10 to 70, with higher scores reflecting better QoL. The SIBQ has been shown to be reliable (Cronbach’s *α* = 0.78) [49].

The *IBD-Control* is used to measure disease control from the patient’s perspective [50]. The IBD-Control questionnaire consists of 13 items and a visual analogue scale, ranging 0-100 (0 = worst control). The 13 items have 3 answer options and include questions about energy, sleep, mood, freedom of discomfort, ability to perform daily activities and treatment concerns. Overall scores ranges from 0 to 26, where lower scores indicates poorer control. The psychometric properties of the IBD-control have been shown to be good (Cronbach’s *α* = 0.85) [50], including the shortened IBD-control-8 version in a Dutch population (Cronbach’s *α* = 0.82) [51].

Clinical disease activity is assessed by clinician-based questionnaires: *Harvey-Bradshaw Index* (HBI) for Crohn’s disease and *Simple Clinical Colitis Activity Index* (SCCAI) for ulcerative colitis [52, 53]. HBI consist of 12 questions about general well-being (score 0–4), abdominal pain (score 0–3), soft stools (1 point per soft stool), abdominal mass (score 0–3) and extra-intestinal manifestations (score 0–1 per manifestation, 8 in total). A flare may be suspected at a score of 5 or higher. SSCAI consist of 9 questions about general well-being (score 0–4), bowel frequency (score 0–2), urgency (score 0–3), rectal blood loss (score 0–3) and extra-intestinal manifestations (score 0–1 per manifestation, 4 in total). In case of a score of 3 or higher, it may indicate a flare.

*Time to flare* is assessed based on the clinical interviews. If a participant reports that they have (had) a flare, the medical record will be tracked. The assessment of the attending physician is leading. A flare is defined by elevated faecal calprotectin levels (> 250 mcg/g) which is validated by a clinical interview plus commencement of any new IBD medication or altered dosing of existing IBD medication. We consider the date of elevated faecal calprotectin levels or change in IBD medication as the start of the flare.

Laboratory tests will be performed every 6 months (T0, T2 and T4), following the regular medical check-ups [54] and extra in case a flare is suspected (HBI ≥ 5, SCCAI ≥ 3). These tests consist of faecal calprotectin, haemoglobin, C-reactive protein and albumin. Having higher levels of faecal calprotectin and C-reactive protein plus low albumin may indicate disease activity [54–56].

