#### Treatment effects at follow-up

In order to investigate consolidation of the treatment effects over time on both the primary outcome (psychological distress) and secondary outcomes (all secondary outcomes except objective sleep parameters) we will again perform linear mixed effect models with time (T1, T2, T3, T4), group (MBCT + TAU versus TAU) and Group*Time interaction, including the same parameters as mentioned above and controlling for baseline levels and stratification variables. Restricted maximum likelihood will be used as estimation method to handle missing data. Cohen’s *d* will be calculated by dividing the adjusted group difference between the means at T4 by the pooled standard deviation at T0.

We also aim to examine the effect of MBCT on recurrence of disease activity (flares). Therefore, we will perform a proportional hazards model (i.e. Cox regression analysis) to analyse the differences between MBCT + TAU and TAU alone in time to flare within the 12-months study period.

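### Time to flare: the only stated trigger for a medical-record check is a flare report by an unblinded participant, so some flares may be missed, possibly unequally by arm

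*Protocol article*

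**What the plan says.** All of the following is from the protocol article.

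- **Source of the endpoint** (IBD-related measures): time to flare "is assessed based on the clinical interviews".
- **Record check** (same paragraph): "If a participant reports that they have (had) a flare, the medical record will be tracked". No other trigger for a record check is given.
- **Event rule** (same paragraph): "The assessment of the attending physician is leading". The next sentence gives a definition: "A flare is defined by elevated faecal calprotectin levels (> 250 mcg/g) which is validated by a clinical interview plus commencement of any new IBD". That sentence ends by naming drug treatment, and a dose change in a drug already taken also qualifies.
- **Onset** (same paragraph): "We consider the date of elevated faecal calprotectin levels or change in IBD medication as the start of the flare".
- **Blinding** (Randomisation and blinding): "Participants cannot be blinded to allocation". On the staff side, the section adds that "the research team has therefore access to the information about the assigned group".
- **Other detection** (Table 1; Procedure and assessments; IBD-related measures): HBI or SCCAI is taken by a clinician at every assessment. A score of at least 5 (HBI) or 3 (SCCAI) prompts extra laboratory tests. Calprotectin is measured in everyone at 6 and 12 months, but at 3 and 9 months only on suspicion of a flare.
- **Analysis** (Treatment effects at follow-up): a Cox model compares the arms on "time to flare within the 12-months study period".

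**The concern.** A time-to-event comparison is fair only if events are found equally well in both arms. Here the step that opens the medical record depends on what a participant says, and the participant knows whether they received MBCT. The protocol's own background makes unequal reporting plausible: it links distress to a stronger experience of physical symptoms and to more care-seeking, and the intervention is meant to change how patients cope with thoughts and feelings.

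Two kinds of flare are at risk of being missed: one that was treated and had settled by the next visit and is not mentioned, and one that occurs after a participant has stopped attending interviews. If the missed share differs by arm, the hazard ratio moves without any difference in disease.

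A second, smaller difficulty is that the Cox model needs one event rule and one date. The article sets physician judgement beside a laboratory-plus-medication definition without saying how they relate, and names two possible onset dates without an order.

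**Working it through.** The documents give no event count, hazard ratio or power for time to flare, so there is no stated figure to reproduce. The main check is a reading of the text; the arithmetic is an illustration.

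**Step 1. Which routes find a flare, and do they lead to the record?**

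| Route | Needs a flare report? | Stated to prompt a record check? | What it can miss |
|---|---|---|---|
| Participant reports a flare at interview | Yes | Yes | Unreported flares; flares after attendance stops |
| Clinician HBI/SCCAI at each assessment | No, but the items (well-being, pain, stools, urgency) are largely reported symptoms | Not stated | Flares settled before the visit |
| Laboratory tests after a high score | No, but depends on that score | Not stated | As above |
| Calprotectin for all at 6 and 12 months | No | Not stated | Flares settled before the sample |
| Adverse event reporting | – | – | Flares are not classed as adverse events (Safety monitoring) |

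The middle three routes apply equally to both arms and reduce the gap. None is said to open the record, and all require attendance. The sample size section allows for 136 − 98 = 38 participants being lost, so flares after last contact are not a trivial category.

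**Step 2. The event rule.** If the physician judges that there was a flare but no calprotectin above 250 was recorded, one reading of the paragraph counts an event and the other does not. If calprotectin is raised and medication is changed but the physician does not call it a flare, the readings differ the other way.

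**Step 3. Illustration of size.**

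Inputs from the Background: cumulative flare rates at 5 years of 69–93% across the quoted ranges. With a constant hazard (assumption), the 12-month risk is p = 1 − (1 − P5)^(1/5):
- 1 − 0.31^(1/5) = 0.209, or 136 × 0.209 ≈ 28 flares
- 1 − 0.07^(1/5) = 0.412, or 136 × 0.412 ≈ 56 flares

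Let sT and sM be the shares of flares found in the TAU and MBCT arms. These are assumptions; the documents give none. With a true hazard ratio of 1:

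observed HR = ln(1 − p·sM) / ln(1 − p·sT)

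Expected events with 68 per arm: D = 68·p·(sT + sM). With μ = √(D/4)·|ln HR|, the rejection rate at two-sided 0.05 is 1 − Φ(1.96 − μ) + Φ(−1.96 − μ).

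Example: p = 0.209, sT = 0.90, sM = 0.70. HR = ln(0.854)/ln(0.812) ≈ 0.76, D ≈ 22.7, rejection rate ≈ 10%.

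To credit the routes that need no flare report, let a share c be found whatever is reported, so s = c + (1 − c) × reported share.

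| Reported share, TAU vs MBCT | c = 0: HR (rejection) | c = 0.5: HR (rejection) |
|---|---|---|
| 95% vs 85% | 0.87–0.88 (6–8%) | 0.93–0.94 (5–6%) |
| 90% vs 70% | 0.73–0.76 (10–18%) | 0.87–0.88 (6–8%) |
| 95% vs 65% | 0.63–0.66 (17–35%) | 0.81–0.83 (8–12%) |

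Swapping the arms gives the reciprocals; for example 1/0.76 ≈ 1.32 and 1/0.73 ≈ 1.37.

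**The case against.** The strongest reply is that detection does not rest on self-report alone. A clinician interviews every participant at each assessment, disease-activity scores are taken each time, high scores lead to laboratory tests, and everyone is sampled at 6 and 12 months. A qualifying flare also involves a treatment start or dose change, and a prescription is harder to forget or reinterpret than a symptom. This stands, and it is why the concern is about a residual gap.

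Four stronger readings are tempting, and the documents do not support them.

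- A reader might infer that records are never opened without a participant's report. The article states one trigger; it does not exclude others.
- A reader might infer that medication changes can be found only in the record. Nothing says so; they could be asked about at interview.
- A reader might infer that the event rules flatly contradict each other. The sentence on the attending physician directly follows the one on the participant's report, and may mean only that the physician overrides the participant, after which the single definition applies. The text is ambiguous.
- A reader might take a hazard ratio from the table as the expected bias. The detection shares have no source, and the direction is unknown.

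It is also fair to say that the order of two onset dates is a detail often left to a full protocol or analysis plan, and that the flare analysis is an additional aim with no power claim.

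**Conclusion.** The point holds in a limited form. The only stated trigger for a record check is a flare report by an unblinded participant, and the other detection routes narrow the gap without being said to close it. Flares that settled between visits, or that followed the end of attendance, can be missed, possibly at different rates by arm.

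The size cannot be derived from the documents. If half of all flares are found regardless of report, the assumed reporting gaps of 10 to 30 percentage points give spurious hazard ratios of about 0.81–0.94 and rejection rates of about 5–12%. The effect is larger if fewer are found that way, and may run in either direction. These figures rest on a constant hazard, 68 per arm and invented detection shares.

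The precedence of physician judgement and definition needs reconciling, but the documents do not show which should prevail, and this review does not choose. The primary HADS analysis is unaffected. Severity: minor.

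**What to change.** 1. At 12 months, check the medical record of every randomised participant in both arms, as far as consent allows, for calprotectin above 250 and an IBD medication start or change, whatever was reported at interview and whether or not the participant still attends.
2. Where existing staff allow, have someone without sight of allocation classify the events.
3. Reconcile the sentence on the attending physician with the calprotectin-plus-medication definition, state which governs the Cox model, and report the other reading as a sensitivity analysis.
4. State which of the two dates counts as onset when both exist.

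**Cost:** at most about 136 record checks across four hospitals, by staff who already check reported flares, plus a few lines of wording. The check looks back at existing records and needs no extra visit or sample.

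**What it leaves open:** outside the scheduled samples, a raised calprotectin is recorded only if someone tested. Events without a sample therefore still depend on testing, which is itself partly driven by symptoms. The sensitivity analysis in item 3 shows how far this matters.
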